**The Netherlands:**

- Wet Medisch–wetenschappelijk Onderzoek met mensen (WMO), 1 december 1999.
- Implementation of EU directive 2001/20/EC into national legislation in The Netherlands is aimed by changing the WMO and the WOG.
- Wet op de Geneeskundige Behandelingsovereenkomst (WGBO), 1 april 1995.
- Wet Bescherming Persoonsgegevens (WBP), 6 juli 2000.
- Wet veiligheid en kwaliteit lichaamsmateriaal (WVKL), 6 februari 2003.

**Sweden:**

- The Ministry of Education and Cultural Affairs; The Act concerning the Ethical Review of Research Involving Humans (2003:460), issued June 5, 2003, and with the following regulations a) Statute (2003:615) concerning the ethical vetting of research involving humans, issued October 9, 2003, b) Statute (2003:616) containing instructions for regional ethical review boards, issued October 9, 2003, and c) Statute

(2003:617) containing instructions for the Central Ethical Review Boards, issued October 9, 2003.

- Ministry of Health and Social Affairs; The Biobanks in Medical Care Act (2002:297), issued May 23, 2002 (Biobankslagen) with the following regulation; Statute (2002:746) concerning biobanks in health care and medical care, issued February 10, 2002.
- Ministry of Justice; The Personal Data Act (1998; 204), issued April 29, 1998 (Personuppgiftslagen, PUL).

#### **Italy:**

- Decreto Legislativo n. 211 del 24 giugno 2003: Attuazione della direttiva 2001/20/CE relativa all'applicazione della buona pratica clinica nell'esecuzione delle sperimentazioni cliniche di medicinali per uso clinico.
- Circolare Ministeriale n. 6 del 2 settembre 2002 : Attività dei comitati etici istituiti ai sensi del decreto ministeriale 18 marzo 1998.
- Decreto del Presidente della Repubblica n. 439 del 21 settembre 2001:Regolamento di semplificazione delle procedure per la verifica e il controllo di nuovi sistemi e protocolli terapeutici sperimentali.
- Decreto Legislativo n. 196 del 30 giugno 2003: Codice in materia di protezione dei dati personali.

#### **Poland**

- ROZPORZADZENIE MINISTRA ZDROWIA I OPIEKI SPOLECZNEJ z dnia 11 maja 1999 r. w sprawie szczegółowych zasad powoływania i finansowania oraz trybu działania komisji bioetycznych. Dz.U. 1999 Nr 47 poz. 480 [Directive of the Ministry of Health of 11 May 1999 on regulations relating to creation, financing and operating activities of bioethical committees. Dz. U. 1999 Nr 47 poz. 480]
- USTAWA z dnia 5 grudnia 1996 r. o zawodach lekarza i lekarza dentysty. Dz.U. 1997 Nr 28 poz. 152. [Directive of 5 December 1996 on the medicine physicians and dental physicians. Dz.U. 1997 Nr 28 poz. 152]
- ROZPORZADZENIE MINISTRA ZDROWIA z dnia 10 grudnia 2002 r. w sprawie określenia szczegółowych wymagań Dobrej Praktyki Klinicznej. Dz. U. 02 nr 221

poz.1864 [Directive of the Ministry of Health of 10 December 2002 on special regulations regarding Good Clinical Practice. Dz. U. 02 nr 221 poz.1864]

- Rozporządzenie Ministra Finansów z dnia 30 kwietnia 2004 r. w sprawie obowiązkowego ubezpieczenia od odpowiedzialności cywilnej badacza i sponsora. Dz. U. 04 nr. 101 poz. 1034 z późn. zm. [Directive of the Ministry of Finance of 30 April 2004 relating to the obligatory insurance for civil responsibility of the sponsor and investigator. Dz. U. 04 nr. 101 poz. 1034 with later changes]

#### **Spain:**

- BOE nº 15 de fecha 17 de Enero de 1996, Ley orgánica 1/96 de 15 de enero de 1996 de PROTECCIÓN JURÍDICA DEL MENOR.

#### **Belgium:**

- Loi du 7 mai 2004 relative aux expérimentations sur la personne humaine. Wet van 7 mei 2004 inzake experimenten op de menselijke persoon. Version coordonnée (août 2003) de la loi relative à la protection des données à caractère personnel du 8 décembre 1992. Gecoördineerde versie (augustus 2003) van de wet van 8 december 1992 tot bescherming van de persoonlijke levenssfeer ten opzichte van de verwerking van persoonsgegevens.

#### **Germany:**

- Gesetz über Medizinprodukte (Medizinproduktegesetz - MPG) 07-08- 2002 (Medical Devices Law).

#### **Norway:**

- Menneskerettsloven av 1999. Biobankloven av 2003. Genteknologiloven av 1993. Personopplysningsloven av 2000.  
All medical research that involves humans (including personal identifiable information and human material) need to be approved by a regional ethics committee. All research that includes handling of personal data, including de-identified information (i.e “avidentifisert”), need to be presented and approved either by an ombud for protection of privacy or the Data Inspectorate.

#### **Israel:**

- Governing Regulations of the Israeli Ministry of Health. 1999 Amendment of Public Health Regulations (Medical Trials in Human Subjects) – 1980

- All clinical studies proposals are reviewed, discussed and approved by the local Helsinki Committee (and ratified by the Human Studies Ethics Committee of the Ministry of Health), which carefully abide to the FDA (USA) and ICH-GCP rules.

**Croatia:**

- Kodeks medicinske etike i deontologije, Narodne novine br. 47, 13.4.2004. (NN 47/04) (Codex of medical ethics and deontology published at Narodne novine No 47, 13th April, 2004).
- Pravilnik o klinickim ispitivanjima i dobroj klinickoj praksi, Narodne novine br 175, 15.10.2003. (NN 175/03) (Regulations on clinical studies and good clinical practice published at Narodne novine No 175, 15th October, 2003).

**Hungary:**

- 1997. évi CLIV. Törvény az egészségügyről. VIII. Fejezet. Az emberen végzett orvostudományi kutatások. 157-164. §
- 23/2002 EüM rendelet az emberen végzett orvostudományi kutatásokról
- 1997. évi LXXXIII. Törvény a kötelező egészségbiztosítás ellátásairól, egységes szerkezetben a végrehajtásáról szóló 217/1997. (XII. 1.) Korm. Rendelettel
- 1997. évi XLVII. eü. Adatvédelmi törvény.
- Comprehensive, EU-conform legislation summary at:  
[http://ec.europa.eu/research/science-society/pdf/hu\\_hong\\_lr.pdf](http://ec.europa.eu/research/science-society/pdf/hu_hong_lr.pdf)

PREVENTCD confirms that the participants will observe the above-specified relevant national rules concerning research with humans, particularly with children.

PREVENTCD confirms that the project will require the approval of the Independent Ethic Committee that governs clinical studies for each participating study site and that they will inform the Commission whether the local, regional or national ethical approval has been obtained before the research to which it relates is carried out.

The Ethics Committee approval or authorisation of a competent body will be specified as a project deliverable.

The population based multicenter study will only involve Swedish participants, and has already been approved by the relevant Regional Ethical Review Board.

### 9.3. Description of the sensitive ethical issues of the proposed research

Identification of the potential ethical aspects of the proposed research:

- 9.3.a. Research on human beings, including: Infants (1,000) and children of school age (16,000) not able to give consent.
- 9.3.b. Human biological samples (e.g. umbilical cord blood, venous blood, small bowel biopsy samples).
- 9.3.c. Human genetic data and personal data.

9.3.a. Research on human beings, including: Infants (1,000) and children of school age (16,000) not able to give consent.

#### *9.3.a.I. Early feeding intervention family study*

A prospective early dietary intervention study of 1000 young children from high-risk families for CD, to assess the possibilities to induce immune tolerance for gluten in genetically predisposed children.

#### Explanation and justification of the research design

The proposed project must necessarily involve infants, and cannot be performed in any other age group, because it is during infancy that the first exposure to gluten takes place and that the immunological response to this antigen occurs and may be modulated. The only way to find out whether the introduction of small quantities of gluten into the diet of infants during the period of breast-feeding does indeed protect against CD is to conduct a double blind prospective randomised study, as the one we here we herewith propose.

#### Informed consent:

Informed consent to participate will be obtained from the parents, guardians or other legitimate representative, as it is usual in the case of young children. The AOECS or the local Coeliac Disease Societies will invite their members with CD expecting a newborn (offspring or sibling) during the next 18 months to participate. All parents, guardians or other legitimate representative of the children, interested to collaborate will be given full information and explanations about the trial and asked to sign a written informed consent form (annexes 2 and 3) by the local responsible physician according to the national legislation. Each parent, guardians or other legitimate representative of the children will receive detailed information about the study procedures, the potential risks and benefits

of the intervention, as well as information about the fundamental rights of a patient included in an experimental study. In addition, care will be taken to inform the patient about the potential benefits of the experimental intervention in a manner that avoids an overestimation of these benefits, by explicitly mentioning that the intervention is fully experimental, that it has no proven efficacy, and that no guarantee can be given that it will work against CD.

These information's will be provided by a physician in charge of the trial, and an informed consent document, preliminarily approved by the relevant ethics committee, will be given to the parents, guardians or other legitimate representative of the children. In case of acceptance by the parents, guardians or other legitimate representative of the children, they/he/she will sign the informed consent document, which will be countersigned by the responsible physician. The signed informed consent form will be archived in the Case Report Form (CRF) at the project office, and a copy will remain with the parents, guardians or other legitimate representative of the child. The parents, guardians or other legitimate representative of the children will always give informed consent by their free will. Only after informed consent is signed will the families be enrolled in the study. The family physician will be duly informed and his standing as the family's health provider will be respected – and relied on for his/her cooperation. The participants may retract from their participation at any moment, also without giving their reasons to do so and without any adverse consequences regarding their relationship with their paediatrician/responsible physician. A copy of both the informed consent form and of the parent's information sheet will be submitted to the pertinent Independent Review Board. No financial reward will be given to participating families at all. Only their real expenses (primarily travel costs), which are related to their accurate participation in the studies, shall be reimbursed. The only exception will be to give a small present to the children: this will not be told to the families in advance, to avoid influencing them in their decision to participate or not.

***Breast-feeding during at least six months will be STRONGLY encouraged to all the families.***

Care for the children and their families during the study

The children and their families will receive frequent and careful medical follow up during

the study (table 1), to ensure their support and their welfare, to ascertain that any undesired effects or symptoms are rapidly detected and that adequate measures are promptly undertaken. In case of health complaints, extra observation will be provided and, if indicated, the participation will be stopped. The main discomfort for the children concerns the blood sampling and the clinical follow up examinations, as detailed in table 1. The risk element involved with this trial concerns that of the performance of small bowel mucosal biopsy in the children with suspected CD. It is again to be stressed that such a biopsy is still the "gold standard" for diagnosing CD, and would be performed only when medically indicated, that is: only in these children with CD antibodies in their serum that indicate gluten sensitivity and are highly suspect for active CD, and NOT just for purpose of the study. Such children would undergo a biopsy also in non-study circumstances. Each centre where the research takes place will make the necessary treatment and infrastructure available to patients who develop trial-related injuries and will provide sufficient insurance to cover subjects for adverse effects directly arising from participation in the trial. All adverse and serious adverse events will be reported according to the regulations cited above.

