| Months                             | Pregnancy | Birth | 1 | 2 | 3 | 4 | 5 | 6 | 7 | 8 | 9 | 10 | 11 | 12 | 14 | 16 | 18 | 20 | 22 | 24 | 28 | 30 | 34 | 36 | 48 |  |
|------------------------------------|-----------|-------|---|---|---|---|---|---|---|---|---|----|----|----|----|----|----|----|----|----|----|----|----|----|----|--|
| Enrolment                          | +         |       |   |   |   |   |   |   |   |   |   |    |    |    |    |    |    |    |    |    |    |    |    |    |    |  |
| Randomisation                      |           |       |   |   | + |   |   |   |   |   |   |    |    |    |    |    |    |    |    |    |    |    |    |    |    |  |
| Intervention                       |           |       |   |   |   | + |   |   |   |   |   |    |    |    |    |    |    |    |    |    |    |    |    |    |    |  |
| Anthropometrics                    |           | +     | + | + | + | + | + | + |   |   | + |    |    | +  |    |    | +  |    |    | +  |    |    |    | +  | +  |  |
| Clinical History                   |           | +     | + | + | + | + | + | + | + | + | + | +  | +  | +  | +  | +  | +  | +  | +  | +  | +  | +  | +  | +  | +  |  |
| Food Questionnaire                 |           | +     | + | + | + | + | + | + | + | + | + | +  | +  | +  | +  | +  | +  | +  | +  | +  | +  | +  | +  | +  |    |  |
| Cord blood Sample Genetic study    |           | +     |   |   |   |   |   |   |   |   |   |    |    |    |    |    |    |    |    |    |    |    |    |    |    |  |
| Breast milk Sample                 |           |       | + | + | + | + | + | + |   |   | + |    |    |    |    |    |    |    |    |    |    |    |    |    |    |  |
| Blood sample Immunological Studies |           |       |   |   |   | + |   | + |   |   | + |    |    | +  |    |    | +  |    |    | +  |    |    |    | +  | +  |  |

- Follow-up 0-4 years: All the children will be frequently controlled for clinical and nutritional assessment and for the presence of immunological markers of gluten (in)tolerance, including determination of serum IgA antibodies against gliadin and tissue trans- glutaminase (tTGA) (table 1). In case of health complaints extra controls will take place and, if indicated, the intervention will be stopped.

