- Diagnosis of CD: The parents of the children with tTGA or symptoms of CD will be offered a small bowel biopsy for the diagnosis of CD. Biopsie will only be performed when medically indicated, that is: only in these children with CD antibodies in their serum that indicate gluten sensitivity and are highly suspect for active CD, and NOT just for purpose of the study. Such children would undergo a biopsy also in non-study circumstances.

A reduction of 50% of CD among the intervention group at the age of 3 will be considered as an effective prevention.
- Power Analysis:(80%, significance level 5%, 2-sided test): Assuming a frequency of 10% CD among the enrolled infants we need to study 474 children randomized to tolerance induction and 474 controls. The number of members of the participating Coeliac Disease Societies (table 3) makes the study feasible.

Table 2. Members of the coeliac disease patient societies collaborating in the project

| CD Societies | Members
(no.) | 0-10 years
(siblings)
(no.) | Female
Fertile age
(mothers) (no) | Male
Fertile age
(fathers) (no.) | Expected newborns to be
recruited
(no.) |
|--------------|------------------|-----------------------------------|-----------------------------------------|----------------------------------------|-----------------------------------------------|
| Netherlands  | 7902             | 1494                              | 670                                     | 390                                    | 150                                           |
| Campania     | 3000             | 800                               | 300                                     | 100                                    | 150                                           |
| Madrid       | 5133             | 2413                              | 387                                     | 162                                    | 100                                           |
| Valencia     | 2050             | 475                               | 152                                     | 67                                     | 75                                            |
| Israel       | 4800             | 800                               | 470                                     | 830                                    | 100                                           |

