### Description of work

- Assessment of the early immune response to gluten in approximately 1000 infants from high-risk families for CD from different European countries. The families will be invited to participate, among others, by the local Coeliac Disease Societies in collaboration with the Association of European Coeliac Disease Societies (AOECS). The CD Societies from the Netherlands (NCV)

([www.coeliakievereniging.nl](http://www.coeliakievereniging.nl)); Campania, Italy ([www.rcm.napoli.it/celiachia](http://www.rcm.napoli.it/celiachia)); Madrid (SCM) ([www.celiacosmadrid.org](http://www.celiacosmadrid.org)), Valencia (ACECOVA), Catalonia (SMAP) ([www.celiacscatalunya.org](http://www.celiacscatalunya.org)), Spain; Israel (CAI), Poland (PCS), Croatia, Hungary ([www.coeliac.hu](http://www.coeliac.hu)) and Germany ([www.dzg-online.de](http://www.dzg-online.de)) will collaborate in the study.

- The Societies will invite to participate their members with CD expecting a newborn (child or sibling) during the next 18 months. Informed consent to participate will be asked from the families by the local responsible physician.
- The children bearing HLA-DQ2 and/or DQ8 will be blindly randomised to either a group for "tolerance induction for gluten" or to a "control" group. At least 6 months of breast-feeding will be STRONGLY encouraged for all the children. At the age of 4 months tolerance induction will be attempted by the daily intake of 1g wheat flour (100 mg gliadin) during 8 weeks while continuing breast-feeding. No gluten will be given in these 8 weeks to control infants, but 1g. lactose as a placebo intervention. Danone will provide the placebo (lactose, Pharmatose) and the intervention product (Glutival obtained from Cargill). Danone has outsourced the production of the sachets with the gluten intervention / placebo products to NIZO Food Research, Ede, the Netherlands. NIZO will prepare and package the gluten intervention product as well as the placebo according to quality criteria adequate for infants aged 4-6 months. Every intervention sachet will be filled 1.8 gr Pharmatose and 0.2 gr Glutival (gluten intervention product); the placebo sachets will be filled with 2 gr of Pharmatose.  

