**Problem II: the bowel biopsies in the intervention study go beyond the minimum burden/risk.**

A small bowel biopsy will only be performed on children participating in the study if there is a medical indication to do so. A small bowel biopsy is the only tool to provide a diagnosis of CD. The biopsies are part of the normal clinical diagnostic routine and are not exclusively used for research purposes in this study. Early identification of CD in high risk populations is an accepted recommendation and should be offered to these high risk children also if they do not participate in the project. This is a crucial aspect, since a diagnostically/medically indicated intervention is not an issue of the Convention. For individuals with elevated immunological blood markers, a biopsy is strongly recommended and medically indicated. There are no limiting recommendations with respect to the children's age for diagnostic biopsies. Because of their high risk for CD 8-10 % (n = 80-100) of the children would undergo a biopsy even without the study.

**Problem III: The dense blood sampling scheme for infants in the intervention study was regarded to be beyond minimum burden/risk.**

The ethically justified blood sampling scheme should not only avoid and limit burden, but should also be of high diagnostic value for the patients and to allow valid scientific results. The consortium will reduce the number of blood samples to seven blood punctures in total (Table 1) and the quantity of blood needed to 5 ml. The number and timing of the blood punctures is such that it will enable to monitor the short and long-time effects of the intervention. At the age of 3 years 10 ml blood will be obtained from the children to allow for determination of additional (auto)immune phenomena related to the development of CD.

**Problem IV: The Swedish population study imposes biopsies on an estimated subgroup of 160 children without direct benefit to them.**

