### **National/local ethical approval of the studies**

The second round of the Swedish population study has already been approved by the regional ethical committee. For the family intervention study the approval of the local ethical committees is a necessary step before the research can start in any of the countries.

A more detailed explanation of the reasons involved in the Executive Summary is exposed below.

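### For health complaints in the family study, one section stops the intervention and another stops participation; read literally, the second ends the follow-up that ascertains coeliac disease

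*Protocol*

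**What the plan says.** Two current sections of the protocol cover the same event in the same study.

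- Section 7.6, Work Package 3, Introduction, under the 0-4 year follow-up: "In case of health complaints extra controls will take place and, if indicated, the intervention will be stopped".
- Section 9.3.a.I, under care for the children and their families: "In case of health complaints, extra observation will be provided and, if indicated, the participation will be stopped".

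Both are triggered by health complaints, both leave the decision to clinical indication, and both refer to Table 1. They differ in what is stopped.

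The surrounding text shows what participation means. The informed consent text of 9.3.a.I says "The participants may retract from their participation at any moment, also without giving their reasons to do so", which is withdrawal from the study. The care paragraph itself later provides insurance for "adverse effects directly arising from participation in the trial".

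The intervention is short: "At the age of 4 months tolerance induction will be attempted by the daily intake of 1g wheat flour (100 mg gliadin) during 8 weeks". Table 1 assessments run to month 48, and effective prevention is defined as a 50% reduction in CD at age 3. Diagnosis starts from serology or symptoms: "The parents of the children with tTGA or symptoms of CD will be offered a small bowel biopsy for the diagnosis of CD".

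**The concern.** If a site stops only the sachets, the child stays under the scheduled clinical and serological checks and the age-3 outcome is still obtained. If a site stops participation, those checks end and the outcome is lost unless it reaches the trial by some route the protocol does not describe.

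The children affected are not a random subset. A health complaint in an infant at high genetic risk may be an early sign of CD or a reaction to the sachet. Removing such children can therefore be related to the outcome, and possibly to the arm. The difference also outlasts the intervention: after about 6 months of age the Work Package 3 rule has nothing left to stop, while the ethics-section rule could still end follow-up. Execution is decentralised across many centres, so different readings are realistic.

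**Working it through.** **Reading the two rules together.** The study, trigger and qualifier are the same, but the thing stopped is not. I looked for text that says which governs, or that keeps a stopped child in follow-up. The provisions on voluntary withdrawal, the safety board and code-breaking for adverse events do neither.

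**What one stopped child loses.** Table 1 schedules immunology blood samples at months 4, 6, 9, 12, 18, 24, 36 and 48, eight in all, of which seven fall by age 3. A child stopped at month 5 has given one. The child misses 8 − 1 = 7 of 8, or 7 − 1 = 6 of the 7 up to age 3.

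**The plan's own sample size.** Inputs from the power analysis in Work Package 3: p1 = 0.10, p2 = 0.05 (the 50% reduction), 80% power, two-sided 5%. With p̄ = 0.075:

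- Uncorrected: n' = [1.960·√(2p̄(1−p̄)) + 0.842·√(p1(1−p1) + p2(1−p2))]² / (p1−p2)² = 434.4, so 435 per arm.
- Continuity-corrected: n = (n'/4)·[1 + √(1 + 4/(n'·0.05))]² = 473.6, so 474 per arm.

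The stated 474 is the corrected figure, so the corrected test is used below:

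power = Φ{ [d − c − 1.960·√(p̄(1−p̄)(1/n1+1/n2))] / √(p1(1−p1)/n1 + p2(1−p2)/n2) }, with d = p1 − p2, c = ½(1/n1+1/n2) and p̄ here the pooled proportion.

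At 474 per arm this gives 80.0%.

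**Scenario 1: equal stopping in both arms.** The protocol gives no stopping rate, so a share s is assumed, with CD risk in stopped children m times the arm average. Then n = 474(1−s), and each arm's rate becomes p(1−sm)/(1−s). For s = 5% and m = 2: n = 450.3, p1 = 0.10 × 0.90/0.95 = 0.0947, p2 = 0.0474, power 75.2%.

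| Share stopped (of 948) | Power, average CD risk | Power, doubled CD risk |
|---|---|---|
| 0 | 80.0% | 80.0% |
| 1% (about 9) | 79.6% | 79.1% |
| 2% (about 19) | 79.2% | 78.2% |
| 5% (about 47) | 77.8% | 75.2% |

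The risk ratio stays at 0.50 throughout.

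**Scenario 2: loss expressed in cases.** The expected cases are 47.4 control and 23.7 gluten. Losing 10% of future cases in each arm removes 4.7 and 2.4, leaving 42.7/469.3 against 21.3/471.6. Power is 75.7% and the risk ratio is still about 0.50.

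**Scenario 3: unequal loss with no true effect.** Start from 47 cases in 474 in each arm and remove cases from one arm only.

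- 2 lost: (45/472)/(47/474) = 0.96 if lost from the gluten arm, 1.04 if from control.
- 5 lost: (42/469)/(47/474) = 0.90 if lost from the gluten arm, 1.11 if from control (p = 0.69, continuity-corrected).

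**The case against.** The strongest reply is that the two sentences can coexist. The Work Package 3 text is the operative procedure. The ethics text is a welfare statement, and the sentence after it names blood sampling and examinations as the child's main discomfort, so an option to end participation makes sense there. It may also simply be loose wording for stopping the sachets.

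The context also works against the literal reading. The care paragraph opens with close Table 1 follow-up, its first response to a complaint is more observation, and it stops only where indicated. Symptomatic children are offered biopsy, and the Problem II text of section 9.3 says that early identification "should be offered to these high risk children also if they do not participate in the project". The trial is double-blind, no mechanism for one-sided loss is documented, and every loss rate above is assumed.

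Most of this stands as a limit on size. It does not remove the conflict. The provisions cited protect the child's clinical care, and none says that CD diagnosed after participation has stopped enters the trial data. Nor can this be left to an analysis plan: whether a child stays under observation is site conduct, and serology that was never drawn cannot be recovered by analysis.

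A further objection is that substituting *intervention* leaves the rule empty after about 6 months of age and removes the physician's stated option to end participation. That is why the change below also lets the physician omit or postpone individual procedures, alongside the parents' existing right to withdraw.

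**Conclusion.** The point holds as a cheap improvement. The protocol states two different stopping rules for the same event and does not reconcile them. Following the ethics-section rule as written would end the scheduled CD ascertainment for children whose complaints may be linked to the outcome.

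The plausible effect is modest. Under equal stopping of 1% to 5%, power falls by between 0.4 and 4.8 percentage points from 80.0% and the risk ratio is essentially unchanged. Unequal loss of 2 to 5 cases would move a null risk ratio to between 0.90 and 1.11. These figures rest on assumed stopping shares, a CD risk in stopped children of one or two times average, and the plan's 10% and 5% rates with 474 per arm. The documents give no stopping rate, so neither the size nor the direction of any bias can be determined from them. The sample size calculation is not in question.

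**What to change.** In section 9.3.a.I, care for the children and their families, change the rule so that the intervention is stopped, as in Work Package 3. In both places add one sentence with two parts:

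- Table 1 follow-up and CD ascertainment continue after the intervention is stopped, unless the parents withdraw consent.
- The responsible physician may omit or postpone any single study procedure, such as a blood draw, that is clinically inadvisable for the child.

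The cost is one changed word and one added sentence in two sections. No visits are added beyond Table 1, though a few more children would be followed on the existing schedule. Because the altered wording is in the ethics section, it may need notification to the local committees; the protocol says of the family study that "the approval of the local ethical committees is a necessary step before the research can start in any of the countries".
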